#### 6.2.9 Prohibited concomitant treatment

Subjects will be advised not to take anti-filarial treatment (Mectizan (ivermectin) or Diethylcarbamazine) or any antihelminthic treatment during the study (including albendazole outside the study treatment). Since the diseases for which ivermectin and DEC are indicated are not prevalent in the study area, it is unlikely that subjects would be prescribed these drugs.

The fact that each follow up is associated with a general medical examination and treatment of common illnesses further reduces the probability of subjects pursuing and getting access to these drugs.

There are no restrictions on other concomitant medication.

At each visit, subjects will be asked about the medication they have taken since the last study drug administration and this will be recorded in the source records and case report form, if available with indication, doses and dates of administration.

## 7 ASSESSMENT OF EFFICACY

### 7.1 Efficacy Variables

The efficacy evaluation will be based on the examination of the slides generated from the calibrated blood smears for the determination of the *L. loa* microfilaria counts.

#### 7.1.1 Primary

The primary efficacy variable is the proportion of subjects in each treatment group whose microfilaria count has been sustainably reduced by 50% from the baseline value at any time point after the first dose. A sustainable reduction by 50% is defined as a reduction to 50% of baseline LLM for at least 4 months.

#### 7.1.2 Secondary

Secondary efficacy variables are:

- The proportion of subjects whose microfilaria counts have been reduced sustainably to <8100 mf/ml after the first dose
  - by treatment group and microfilaria strata
  - by treatment group stratified by gender
  - by treatment group stratified by gender and initial microfilaria count
- The percent reduction in microfilaria counts at each time point quantitated via the range, William geometric mean and median
  - by treatment group across all patients
  - by treatment group stratified by initial microfilaria count
  - by treatment group stratified by gender
  - by treatment group stratified by gender and initial microfilaria count
- The evolution of *Loa* parasitemia with time in each treatment group analysed via General Linear Model

### 7.2 Method and timing of measurement of efficacy parameter

The method of parasitological examination at screening and at each efficacy follow up will be the calibrated blood smear (CBS). This examination will be done by finger prick after a careful cleaning of the finger. The blood will be collected with a 50µl non-heparinized capillary tube, spread on a labeled slide, dried and stained. More details are provided in section 6.1.7.1.

Blood samples for baseline LLM as well as for all efficacy follow up evaluations (at M2, M4, M6, M8, and M10, and at M 14 and M18) will be obtained between 11:00 and 15:00 o'clock.

The date and time of day of the collection of a blood sample will be recorded and visits will be planned in a way that each village is visited at the same time of day throughout the study.

In a previous study determining *L. loa* periodicity in subjects who had developed adverse effects after treatment with ivermectin and in control subjects (Kamgno et al., 2004, Figure 1), the *Loa* parasitemia was relatively stable (variation ≤20%) between 11:00 and 15:00.

Collection of samples between 11:00 and 15:00 in combination with scheduling visits to a particular village for the same time of day will ensure that the results will be comparable between and within the groups and that diurnal variation will not compromise the efficacy analysis.

## **8 ASSESSMENT OF SAFETY**

### **8.1 Safety Variables**

All safety variables will be derived from the adverse events reported by the subjects and/or observed during the clinical evaluations.

The frequency of treatment emergent adverse events will be compared by type of adverse event, severity and relationship to study drug between treatment groups.

Serious adverse events will be tabulated by relationship to study drug and treatment group. Narratives will be provided for each event.

### **8.2 Methods and timing for assessing adverse events**

Follow up for adverse events will be conducted on the day of treatment, at day 3 and day 7 after each treatment as well as at the next treatment or efficacy follow up visit (M2, M4, M6, M8, and M10, and at M 14 and M18. Adverse events will also be determined through the clinical examination conducted prior to each treatment, and if clinically indicated through laboratory evaluations. If clinically indicated or indicated based on the report of adverse event(s) by the subject, a complete blood count and laboratory evaluations will be performed as appropriate.

Any study related adverse events will be treated either in the village by the study team or in a hospital or treatment center to which the subject will be transferred if the adverse event cannot be treated in the village by the study team. A district medical officer is part of the study team.

If any non study related adverse events are diagnosed during the clinical examination the subjects will either be treated by the study team if this is within the capacity of the study team or they will be referred to a hospital or treatment center.

In both cases the investigator will discuss with the subjects their continued participation in the study. If this is not consistent with the well being of the subject, the investigator will withdraw the subject from further treatment or from the whole study.

For each adverse event the following information will be recorded:

- Subject number, subject initials, randomization number
- Type of adverse event
- Start date and time
- End date and time
- Severity (see section 8.4)
- Whether the adverse event is due to a pre-existing condition (ie, an acute condition present at the start of the study or history of a chronic condition), and was present prior to study start or study treatment
- Relationship to study treatment (see section 8.5).
- Action taken;
- Outcome.

All adverse events will be followed up to resolution or until a study-unrelated cause has been established.

The methods for clinical examination and laboratory tests for ALT, AST, creatinine and haemoglobin and pregnancy are described in section 6.1.7.2 and 6.1.7.3.

Other laboratory tests will be conducted if clinically indicated.

### 8.3 Adverse event definitions

#### 8.3.1 Adverse event

An **adverse event** is defined as any untoward, undesired, unplanned clinical event in the form of signs, symptoms, disease, or laboratory or physiological observations occurring in a human being participating in a clinical study with a study drug, regardless of causal relationship. This includes the following:

- Any clinically significant worsening of a preexisting condition.
- Any recurrence of a preexisting condition.
- An AE occurring from overdose of a study drug whether accidental or intentional (ie, a dose higher than that prescribed by a health care professional for clinical reasons).
- An AE occurring from abuse of a study drug (ie, use for nonclinical reasons).
- An AE that has been associated with the discontinuation of the use of a study drug.

Note: A procedure is not an AE, but the reason for a procedure may be an AE.

#### 8.3.2 Treatment emergent adverse events

Treatment emergent adverse events are adverse events that occur after administration of the study drug.

#### 8.3.3 Serious adverse event

A **serious adverse event** (SAE) is any AE occurring at any dose that meets 1 or more of the following criteria:

- Results in death
- Is life threatening  
The term 'life-threatening' refers to an event in which the subject was at risk of death at the time of the event. It does not refer to an event, which hypothetically might have caused death, if it were more severe.
- Requires inpatient hospitalization or prolongation of an existing hospitalization  
In general, hospitalization signifies that the subject has been detained (usually involving at least one overnight stay) at the hospital or emergency ward for observation and/or treatment that would not have been appropriate in the physician's office or out-patient setting. Complications that occur during hospitalization are AEs. If a complication prolongs hospitalization or fulfills any other serious criteria, the event is 'serious'. When in doubt as to whether 'hospitalization' occurred or was necessary, the AE should be considered 'serious'. Hospitalisation for elective treatment of a pre-existing condition that did not worsen from baseline is not considered an AE.
- Results in a disability / incapacity  
The term disability means a substantial disruption of a person's ability to conduct normal life functions. This definition is not intended to include experiences of relatively minor medical significance such as uncomplicated headache, nausea, vomiting, diarrhoea, influenza and accidental trauma (e.g. sprained ankle) which may interfere or prevent everyday life functions but do not constitute a substantial disruption.
- Results in a congenital anomaly or birth defect

If there is any doubt if an event is an AE or SAE, the event is to be classified as an SAE.

#### 8.4 Assessment of severity of adverse events

The severity of adverse events will be graded as

|                 |                                                                                                                           |
|-----------------|---------------------------------------------------------------------------------------------------------------------------|
| Mild:           | An event that is easily tolerated by the subject, causing minimal discomfort and not interfering with everyday activities |
| Moderate:       | An event that is sufficiently discomforting to interfere with everyday activities                                         |
| Severe:         | An event that prevents normal everyday activities                                                                         |
| Not applicable: | Events where intensity is meaningless or impossible to determine (i.e. blindness and coma).                               |

#### 8.5 Assessment of relationship of adverse event to study drug

When assessing the relationship between administration of a study drug and an AE, the following should be considered:

- Temporal relationship between administration of the study drug and the AE
- Biological plausibility of relationship (i.e. consistent with the pharmacological action of the drug)
- Subject's underlying clinical state (concurrent illness, relevant medical history) or concomitant agents and/or therapies
- When applicable, whether the AE decreases in severity on discontinuation of the study drug (dechallenge)
- When applicable, whether the AE reappears or increases in severity on repeat exposure to the study drug (rechallenge, Note: a subject should not be re-administered a drug if there is a suspicion that the drug may have caused an adverse event and there is no reason to believe that the benefit for the patient from the rechallenge outweighs the potential risk of the AE if it is indeed causally related to the drug administration)

| Reasonable possibility of relationship to study drug | Criteria
The adverse event                                                                                                                                                                                                                                                                          |
|------------------------------------------------------|--------------------------------------------------------------------------------------------------------------------------------------------------------------------------------------------------------------------------------------------------------------------------------------------------------|
| Yes                                                  | Has a reasonable temporal association with study drug administration
And/or follows a known response pattern to the study drug
And could or could not have been produced by other factors such as the subject's clinical state, therapeutic intervention or concomitant therapy    |
| No                                                   | The event was most probably produced by other factors such as the subject's clinical state, therapeutic intervention or concomitant therapy
OR
The event is clearly related to other factors such as the subject's clinical status therapeutic intervention or concomitant therapy |

## 8.6 Reporting of serious adverse events and pregnancies to GSK, TDR and National regulatory authorities

All AEs and SAEs will be recorded on source documents and recorded on CRFs.

### 8.6.1 Serious adverse events

All SAEs will be reported by the PI on the SAE reporting forms to GSK, and to the National regulatory authorities as per their requirements within 24 hours of the investigator learning about them. The investigator has to provide follow-up information concerning the outcome independent on whether the subject was discontinued from the study due to the pregnancy or other reasons.

The SAE reporting forms in the Attachment include the information to be provided. The filled out forms will be faxed to:

|                                                                   |               |                        |
|-------------------------------------------------------------------|---------------|------------------------|
| GSK Global Clinical Safety & Pharmacovigilance (GCSP): | FAX    | [name] |
|                                                                   | PHONE: | [name] |

### 8.6.2 Pregnancies

All pregnancies that occur during the study will be reported to GSK within 2 weeks of the investigator learning about them on the form provided in the Attachments.

When possible, all reports of pregnancy must be followed up for information about the course of the pregnancy and delivery, as well as the condition of the newborn and the data reported to GSK on the form provided in the Attachments. The filled out forms will be faxed to the same fax number as the SAE information.

## 9 DATA ANALYSIS

### 9.1 Sample Size Justification

A positive response in a subject is defined as a drop in LLM from baseline values by  $\geq 50\%$  lasting at least 4 months. Assuming that in the population less than  $1/10^6$  subjects will have a positive response if randomized to the placebo group and at least 50% of the subjects will have a positive response if randomized to the 6 dose albendazole treatment regimen, a sample size of 16 subjects in each treatment arm will provide at least 90% power to detect statistically significant (two-sided  $\alpha=0.025$ ) differences between the placebo group and the 6 dose albendazole treatment group. The same assumptions were made for the 2 dose albendazole treatment regimen so that the same power and sample size considerations apply to the comparison between placebo and the 2 dose albendazole treatment. An alpha value of 0.025 was chosen since two comparisons (placebo vs. 2 doses of albendazole, placebo vs. 6 doses of albendazole) will be performed. Based on prior experience, a drop out rate of approximately 20% is expected, resulting in a sample size of 20 subjects for each of the three treatment arms.

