**Table 2 Overview of effect of albendazole treatment on *Loa loa* microfilaremia**

| Albendazole regimen (number of subjects)                                                           | Pre-Tx LLM (mf/ml)
Time of measurement
Range (Geom. Mean)                            | Efficacy (% geometric mean preTx values)                                                                                                              | Adverse events                                                                 |
|----------------------------------------------------------------------------------------------------|--------------------------------------------------------------------------------------------|-------------------------------------------------------------------------------------------------------------------------------------------------------|--------------------------------------------------------------------------------|
| 200 mg BID, 21 days (11)                                                               | 11:30-14:30
385 - 20200 (2369)                                                          | - 70%-20% over 3 mos post Tx start
- 20% at 6 mos                                                                                                  | Myalgia, arthralgia, pruritus, increased appetite, dizziness, calabar swelling |
| Placebo BID, 21 days (12)                                                                          | 236 - 27500 (3119)                                                                         | - 37%-192% over 3 mos post Tx start
- 84% preTx at 6 mos                                                                                           | Myalgia, arthralgia, pruritus, increased appetite                              |
| 600 mg, single dose (23)                                                               | 11:00 - 13:00
7 - 1377 (180)                                                            | - 60%-125% over 3 mos post Tx start
- 60% at 6 mos
- 57% at 10 mos                                                                              | No adverse events reported                                                     |

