## 5.2 Primary endpoint

The primary endpoint will be the proportion of subjects in whom there is a sustainable ( $\geq 4$  months) reduction in microfilaremia by  $\geq 50\%$  of pretreatment values at any time point post the first drug administration by treatment group.

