### 6.2.2 Choice of control treatment

Three of the studies conducted to date evaluated the effect of different dosing regimens of albendazole on loiasis microfilaremia in comparison to no treatment.

The data from the subject groups who received no treatment show that *Loa loa* microfilaremia can vary significantly over time without any treatment. Klion et al. (1993) reported that geometric mean microfilaria levels in the placebo group varied between 32% and 192% of pretreatment levels over the 6 months follow up time without a consistent trend and including a drop from 192% to 84% of pretreatment values within a period of 3 months. The data from the study of Tsague-Dongmo et al (2002) showed among subjects with pretreatment levels >8000 mf/ml variations of microfilaria levels of between 73% and 114% of pretreatment values over a period of 9 months, including a drop by 30% over a period of 30 days (see Table 2).

The inclusion of a placebo group is consequently required to assess whether any of the two albendazole treatment regimens is effective, i.e. to see whether any changes in the treatment arms receiving albendazole are actually albendazole-associated and/or larger than the natural longitudinal variation of microfilaria counts as observed in the placebo group. This in turn is the prerequisite for planning further steps to qualify a multiple dose albendazole regimen for reduction of LLM on a community treatment basis.

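### The stated power of at least 90% holds only if about 2% or fewer of placebo subjects respond; the assumed rate below one in a million is unsourced and does not fit section 6.2.2

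*Protocol*

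**What the plan says.** Section 9.1 of the protocol, and the same text in the tabular overview under the rationale for the number of subjects, assume that "less than $1/10^6$ subjects will have a positive response if randomized to the placebo group" and that "at least 50% of the subjects will have a positive response if randomized to the 6 dose albendazole treatment regimen". From this they conclude that "a sample size of 16 subjects in each treatment arm will provide at least 90% power". The test level is explained by "An alpha value of 0.025 was chosen since two comparisons", and the same assumptions serve the two-dose comparison. A dropout of about 20% takes 16 to 20 per arm. No source is given for the placebo rate, and power is not shown for any other value.

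A responder is a subject whose count falls by at least half from baseline and stays there for at least 4 months. Section 5.2 lets this occur "at any time point post the first drug administration by treatment group". There are seven follow-up counts (months 2, 4, 6, 8, 10, 14 and 18), compared with one baseline count taken on the first treatment day (section 6.1.3.5).

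Section 6.2.2 describes natural variation. In one earlier trial "geometric mean microfilaria levels in the placebo group varied between 32% and 192% of pretreatment levels"; Table 2 gives the same group as "37%-192% over 3 mos post Tx start". An untreated subgroup above 8000 mf/ml ranged from 73% to 114%. Sections 6.2.2 and 11.6 both give this variation as the reason a placebo group is needed.

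**The concern.** One part of the protocol says untreated counts vary enough that a control group is indispensable. Another sizes the trial as if that variation could produce practically no responders. The endpoint is open to chance responders: any qualifying stretch over 18 months counts, and after month 10 two readings are enough to span 4 months (months 10 and 14, or 14 and 18). A baseline that happens to be high lowers every later percentage for that subject.

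The power figure is the only justification of size, and it covers both comparisons with placebo. Section 4 makes a difference from placebo the condition for discussing further studies. A null result read against an unconditional 90% would carry more weight than the design can give it.

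**Working it through.** **Inputs.** Section 9.1: 16 evaluable per arm, two-sided level 0.025, albendazole response 0.50, placebo response below 0.000001. Section 9.2.1: chi-square test of each active arm against placebo. The protocol does not mention a continuity correction, so the uncorrected test, which gives the highest power, is used.

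**Step 1: reproduce the stated figure.** With placebo response effectively zero, the placebo count is 0/16. For counts a (placebo) and b (albendazole), chi-square = 32 × (16b − 16a)² / [16 × 16 × (a+b) × (32−a−b)], and the critical value is 5.024.

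- 4/16 against 0/16: 4.57, not significant.
- 5/16 against 0/16: 5.93, significant.
- Power = P(X ≥ 5) for Binomial(16, 0.5) = 1 − 2517/65536 = 96.2%.

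With a continuity correction or Fisher's exact test the threshold is 6/16, and power is 1 − 6885/65536 = 89.5%. The normal approximation also gives 89.5%. Dropout: 16/0.8 = 20. The stated figure therefore reproduces, within rounding, by every method.

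**Step 2: change only the placebo rate.** For placebo counts of 0, 1, 2, 3 and 4, the smallest significant albendazole counts are 5, 7, 8, 10 and 11. Their probabilities at 50% response are 0.962, 0.773, 0.598, 0.227 and 0.105. Power is the sum of these, weighted by the probability of each placebo count. At 5% placebo response the weights are 0.440, 0.371, 0.146, 0.036 and 0.006:

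0.440 × 0.962 + 0.371 × 0.773 + 0.146 × 0.598 + 0.036 × 0.227 + 0.006 × 0.105 = 0.806

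Full enumeration gives:

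| Placebo response | Power, 16 per arm | Power, 20 per arm |
|---|---|---|
| 0.000001 | 96.2% | 99.4% |
| 1% | 93.1% | 98.1% |
| 2% | 90.1% | 96.4% |
| 5% | 80.6% | 89.4% |
| 10% | 63.5% | 74.2% |
| 15% | 46.7% | 57.3% |

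With 16 per arm, power falls below 90% once placebo response passes about 2.0%. At 10% placebo response, 90% power needs a true albendazole response of 65.9%. Fisher's exact test would give 67.8%, 49.0% and 33.3% at 5%, 10% and 15%.

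**Step 3: what placebo rate could the endpoint produce?** The protocol gives no individual rate, so this step is illustrative and rests on assumed values. Untreated counts were simulated as log-normal around a stable level, at the planned visits, with autocorrelation times from 0 to 12 months. A response was a run of visits spanning at least 4 months, all at or below half of baseline.

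| Assumed within-subject SD (log scale) | Placebo responders |
|---|---|
| 0.2 | 0.1–0.3% |
| 0.25 | 0.5–1.3% |
| 0.3 | 1.6–3.3% |
| 0.4 | 6–9% |
| 0.5 | 10–15% |

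Even at 0.2 the rate is at least 0.001/0.000001 = 1000 times the assumed ceiling. The 2% boundary is reached near an SD of 0.3.

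**The case against.** The strongest reply is that nothing cited shows a sustained response in a single placebo subject. The figures in section 6.2.2 are group geometric means at single visits. The group that fell to 32% (37% in Table 2) was back at 84% by month 6, had 12 subjects, and started from a geometric mean of 3119 mf/ml, whereas this trial enrols only above 15000. The closer comparison, the subgroup above 8000 mf/ml, never fell below 73%. The placebo groups of the crossover trial in Table 2 stayed between 95% and 110% over three months and then rose to about 120% or more. All of this stands. A reader might infer that the earlier data directly disprove the assumed rate, or that they establish a placebo response of 5% to 15%. The protocol supports neither. A within-subject SD cannot be recovered from group means either, because the answer depends on which visit and which group are chosen.

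The measurement safeguards also count. Baseline is re-measured on the first treatment day, which limits regression to the mean from selecting high screening counts. Samples above 30000 mf/ml are spread over two slides, slides are re-read blind, and sampling times are held constant within each village. These steps reduce selection effects, counting error and diurnal error. They do not remove the longer-term variation on which section 6.2.2 relies.

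Finally, the amendment records that follow-up reached month 18 and the blind was lifted, so new wording cannot alter the conduct of the trial. It can still alter how a null comparison is read. That such a result would be taken as proof of no effect is a risk, not something the protocol says.

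**Conclusion.** The point holds as an unsupported planning assumption of moderate importance. A reader might take it for an arithmetic error; it is not, since the stated power follows from the stated inputs. What fails is the placebo input: it has no source and cannot be reconciled with the protocol's own account of natural variation or with an endpoint that may be met at any of several visits.

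With 16 evaluable per arm, 50% response on albendazole, two-sided 0.025 and the uncorrected chi-square test, about 90% power survives up to a placebo response of 2%. Beyond that it drops to 81%, 64% and 47% at 5%, 10% and 15%. Those three rates are assumptions. The protocol does not show that the trial is underpowered, only that its power is conditional on a rate it does not know.

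**What to change.** In section 9.1 and in the tabular overview, remove the unconditional claim of at least 90% power and the one-in-a-million premise. Replace them with wording such as:

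*With 16 evaluable subjects per arm, a 50% response on albendazole, two-sided alpha 0.025 and the uncorrected chi-square test, power is about 96%, 93%, 90%, 81%, 64% and 47% for a placebo response of 0%, 1%, 2%, 5%, 10% and 15%. If all 20 per arm are evaluable, it is 89%, 74% and 57% at 5%, 10% and 15%. At 10% placebo response, a true albendazole response of about 66% is needed for 90% power with 16 per arm. No individual rate of sustained placebo response was available at planning.*

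No subjects are added, and the endpoint and test are unchanged. The cost is one paragraph in two places and a less favourable stated power.

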### 9.2 Statistical Methods

#### 9.2.1 Efficacy analysis

Proportions of patients with a sustained reduction of LLM from baseline by  $\geq 50\%$  between each active treatment group and the placebo group will be compared by the Chi square test.

*Loa* parasitaemia will be compared at each point between groups using non-parametric test due to the non normal distribution of the *Loa* microfilaraemia. The General Linear Model (GLM) will also be used for the comparison of the evolution of *Loa* parasitemia in different groups.

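### The fixed 0.025 per comparison is valid, but Holm's step-down rule would recover power on the second placebo comparison without extra subjects (optional improvement)

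*Protocol*

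**What the plan says.** Section 9.1 of the protocol and the sample-size row of the tabular overview fix the multiplicity rule. Two comparisons are named ("placebo vs. 2 doses of albendazole, placebo vs. 6 doses of albendazole) will be performed"), and each is sized to "detect statistically significant (two-sided" alpha 0.025) differences, with the reason "An alpha value of 0.025 was chosen since two comparisons" are made. The planning rates are a placebo response below one in a million and at least 50% on six doses. For the other arm, "The same assumptions were made for the 2 dose albendazole treatment regimen".

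The claimed result is that "a sample size of 16 subjects in each treatment arm will provide at least 90% power to detect statistically significant" differences, and "a drop out rate of approximately 20% is expected, resulting in a sample size of 20 subjects for each of the three treatment arms".

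Section 9.2.1 says that the proportions of responders "between each active treatment group and the placebo group will be compared by the Chi square test". It does not say whether a continuity correction applies. Neither section has a step-down, hierarchical or other rule that passes alpha on after a first rejection.

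**The concern.** Under a fixed split, the second regimen must reach 0.025 even when the first is already significant. Once one null hypothesis has been rejected at 0.025, only one remains, and it can be tested at 0.05 without raising the family-wise error above 5%. The fixed split leaves that alpha unused.

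The second comparison matters here. Section 4 asks whether one or both regimens are effective enough to become candidates for mass treatment, so a verdict on each is wanted. Section 9.1 also assumes that two doses work as well as six. If two doses do less well, the 2-dose comparison is the one short of power, and it is the one a step-down rule would help.

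**Working it through.** **Inputs.** From Section 9.1: two-sided 0.025 per comparison, 16 evaluable per arm, response rates 0 (stated as below 1 in 10^6), 50% and 50%, 20% dropout. From Section 9.2.1: chi-square test of each active arm against placebo. All other response rates below are assumptions.

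**1. The plan's own figure.** For two proportions with pooled variance,

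n = [z(0.9875)·√(2p̄(1−p̄)) + z(0.90)·√(p1(1−p1)+p2(1−p2))]² / (p2−p1)²,

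with z = 2.241 and 1.282, p1 ≈ 0, p2 = 0.5 and p̄ = 0.25. This gives n = 16.2, or 17 after rounding up. The approximate power at 16 is 89.5%. The stated 16 per arm is reproduced to within rounding, and 16/0.8 = 20 enrolled.

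**2. Cut-offs at 16 per arm against 0/16 on placebo.**

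| Test | Responders needed at 0.025 | Responders needed at 0.05 |
|---|---|---|
| Pearson chi-square, uncorrected | 5 (p = 0.0149) | 4 (p = 0.0325) |
| Fisher's exact | 6 (p = 0.0177) | 5 (p = 0.0434) |
| Chi-square with Yates correction | 6 (p = 0.0235) | 6 (5 gives p = 0.0515) |

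**3. Power under the planned rates.** With no placebo responders the two comparisons depend on independent counts X2 and X6, each binomial(16, 0.5). The total number of outcomes is 65,536.

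- P(X ≥ 4) = 1 − 697/65,536 = 0.9894
- P(X ≥ 5) = 1 − 2,517/65,536 = 0.9616
- P(X ≥ 6) = 1 − 6,885/65,536 = 0.8949
- P(X = 4) = 1,820/65,536 = 0.0278
- P(X = 5) = 4,368/65,536 = 0.0667

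Uncorrected chi-square:
- Both significant, fixed split: 0.9616² = 0.925.
- Both significant, Holm (both at least 4, at least one at least 5): 0.9894² − 0.0278² = 0.978.
- One given comparison: 0.962 under the fixed split; 0.9616 + 0.0278 × 0.9616 = 0.988 under Holm.
- At least one significant: 1 − (1 − 0.9616)² = 0.9985 under either rule.

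Fisher:
- Both significant: 0.8949² = 0.801 under the fixed split; 0.9616² − 0.0667² = 0.920 under Holm.
- One given comparison: 0.895 under the fixed split; 0.8949 + 0.0667 × 0.8949 = 0.955 under Holm.
- At least one significant: 0.989 under either rule.

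Yates: 6/16 is needed at both levels, so nothing changes (0.895 per comparison, 0.801 for both).

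**4. If two doses work less well (assumptions).** With a 2-dose response of 30%, P(X2 ≥ 5) = 0.550 and P(X2 = 4) = 0.204. Holm's 2-dose power is then 0.550 + 0.204 × 0.9616 = 0.746. Full enumeration of the three arms with the shared placebo arm gives the following.

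| 2-dose / 6-dose / placebo, 16 per arm | Quantity | Chi-square, fixed → Holm | Fisher, fixed → Holm | Yates, fixed → Holm |
|---|---|---|---|---|
| 30% / 50% / 0 | 2-dose power | 0.550 → 0.746 | 0.340 → 0.528 | 0.340 → 0.340 |
| 30% / 50% / 5% | 2-dose power | 0.318 → 0.461 | 0.181 → 0.286 | 0.178 → 0.201 |
| 50% / 50% / 10% | both significant | 0.474 → 0.616 | 0.312 → 0.407 | 0.282 → 0.377 |

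**5. Error rate.** When all three arms are equal, any false rejection requires the smaller p-value to pass 0.025, so the two rules agree by construction (0.038 at a common 20%, chi-square). The informative case is one working regimen and one that equals placebo. The false-positive rate of the ineffective regimen, 16 per arm, is:

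| Ineffective / working / placebo | Chi-square, fixed → Holm | Fisher, fixed → Holm |
|---|---|---|
| 20% / 80% / 20% | 0.021 → 0.047 | 0.007 → 0.015 |
| 30% / 90% / 30% | 0.025 → 0.053 | 0.010 → 0.017 |

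The 0.053 arises because the uncorrected chi-square does not quite hold its level at this size. Holm adds no error beyond that of the component tests.

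**The case against.** The strongest reply is that nothing here is wrong. A fixed 0.025 for each of two comparisons controls the family-wise error, the reason is stated, and the sample size is consistent with it. Section 9.2.1 names a test but no decision threshold, so a step-down refinement could sit in an analysis plan that is not at hand. Under the planned rates the per-comparison gain with the uncorrected chi-square is under 3 points. The larger gains need response rates that the protocol does not give, and with the Yates correction at 16 per arm and no placebo responders the gain is nil. All of this stands, and it makes the point an optional efficiency gain.

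Three stronger readings are tempting, and the documents support none of them:

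- A reader might infer that the trial's multiplicity control or sample size is faulty. Both are sound as stated.
- A reader might infer that a useful 2-dose regimen would be wrongly dropped for missing 0.025. No section drops a regimen on a p-value; Section 4 sends efficacy and safety results to a discussion with stakeholders. Nor does the protocol call the 2-dose regimen the more practical one. Section 6.1.6.3 says only that compliance with multiple doses is a challenge.
- A reader might infer that the change is free in error terms. The family-wise limit stays at 5%, but an ineffective regimen's false-positive rate can roughly double when the other regimen works.

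**Conclusion.** The fixed split is valid but dominated in power: Holm rejects everything it rejects and sometimes more, with the same sample size and the same first-step threshold. Under the plan's own rates at 16 per arm, the gain for showing both regimens is about 5 points (uncorrected chi-square) or 12 points (Fisher), and about 3 or 6 points per comparison. Gains near 20 points for the 2-dose arm rest on an assumed 30% response with no placebo responders. The chance of at least one significant regimen is the same under both rules. Family-wise control at 5% requires each test to hold its level, which the uncorrected chi-square does only approximately at this size. This is an optional improvement; no error in the plan is shown.

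**What to change.** In Sections 9.1 and 9.2.1 and in the tabular overview, state that the two placebo comparisons are tested by Holm's procedure at an overall two-sided 0.05: the smaller p-value at 0.025 and, if significant, the larger at 0.05. Preferably name an exact test in Section 9.2.1; at the least, say whether a continuity correction is used, because the benefit depends on it.

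The change costs one sentence and no subjects or visits, and the sample-size calculation can stay. The statistical price is the higher false-positive rate for an ineffective second regimen, from about 2.5% towards 5%. The rule must be fixed before unblinding. The protocol amendment records that the blind was lifted at 18 months, so it could not be introduced after that point as a confirmatory rule.
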